### Outcomes

*Primary outcome:* The proportion of refrigerators with vaccine vials within the target range (+2 °C to +8 °C) during a 7-day monitoring at 5-minute intervals after 6 months. Temperature inside the target range is chosen as the primary outcome, because it is of utmost importance that nonfreezing vaccines are stored in this temperature range. When absorbed mono- and combination vaccines reach their individual freezing thresholds, their chemical structures irreversibly change. This can lead to increased local reactions and reduced effectiveness. The most sensitive vaccines are hepatitis B vaccines with a freezing threshold of -0.5 °C [2]. A thermal analysis of frequently used types of refrigerators by the US Department of Commerce [22, 23] showed that vaccine vial temperatures vary depending on the refrigerator type, loading density and location of vaccines inside the refrigerator. Typical refrigerators used in German primary care are the types “freezerless” (single refrigerator compartment without a freezer) and “dual zone” (separate compartments for refrigerator and freezer, both with individual doors), both so-called domestic refrigerators. Based on different scenarios, that is, door openings and loading density, temperatures can vary by +/-2.3 °C in the type “freezerless” and by +/-4.5 °C in the type “dual zone” [22, 23]. The maintenance of the temperature range of +2 to +8 °C, as recommended by vaccine manufacturers and public health authorities worldwide, is hence justified and therefore serves as a primary outcome measure.

Temperatures will be measured via a data logger that is approved by the US Center for Disease Control (CDC), and the same type will be distributed to each practice in order to ensure consistency of temperature readings across locations. Continuous measurements over 7 days are planned for baseline (t0) and continuously thereafter, with follow-ups after 6 months (t2), 1 year (t3) and 18 months (t4). Continuous measurements are preferable to single-point measurements because many practices use nonpurpose built refrigerators (so-called domestic refrigerators). Such refrigerators are known to have temperature cycles that result from their on-/off-construction: using the physical principle of the Carnot cycle, they cool down to a specific temperature, after which the cooling department is shut off until a higher temperature is reached [22, 23]. To analyze such temperature fluctuations, we chose a logging interval of one reading every 5 minutes. Similar logging rates were used in prior studies [12, 14, 17, 19, 20]. The logging period of 7 days ensures that at least one regular working week and one weekend are included. This takes differences in patient flow and refrigerator door openings into account (for example, typically more patients on Mondays).

*Secondary outcomes* follow international best practices and guidelines:Temperature monitoring - Improvement in temperature monitoring with optimal monitoring defined as electronic or paper-based recording with a minimum of two readings per day for the previous 5.5 months (5 % missing entries allowed). Prior studies indicated that temperature fluctuations without adequate adjustments over time are a main barrier to intervention success. To overcome this barrier, this intervention program will emphasize temperature monitoring, including temperature reviewing, recording, taking immediate action if needed and retention of temperature logs.Refrigerators not freezing - The proportion of practices with vaccine vials not reaching critically low temperatures (-0.5 °C or lower) will be determined.Compliance with storage recommendations - Improvement in actual refrigerator-related storage quality will be assessed at practice level according to the following examples:Refrigerator is used exclusively for vaccine storage.Standard thermometer is located in refrigerator.No vaccines are stored in refrigerator door.Vaccines are stored in their original wrapping.e Vaccines are stored in the center of the refrigerator.Use of a stock management system (for example, “earliest expiry first out (EEFO)” principle) and regular manual stock control.4.Knowledge about vaccine storage - Improvement in knowledge of good vaccine storage conditions in physicians and practice personnel will be studied using a standardized questionnaire.5.Assignment of personnel - During the initial practice visit the study assistant will ask if practices currently have assigned personnel as vaccine storage manager and backup. This is considered an important structural characteristic to maintain long-term changes at practice level.

### Measurement instruments

#### Temperature data logging

An important distinguishing factor from previous studies, but in line with international best practices [5–7], is the use of a data logger with one high-accuracy thermistor probe immersed in glycol. In contrast to a standard air probe, the slow-reacting glycol probe resembles the temperature changes of the vaccine vials, whereas the fast-reacting air probe only shows the ambient air temperatures inside the refrigerator and the effects of door openings on refrigerator temperatures.

Specifications and set-up of the chosen data logger are described below:Type - EL-GFX-DTP.Manufacturer - Lascar Electronics Ltd, UK.Probe - High-accuracy thermistor probe immersed in glycol.Accuracy for probe within the operating range -5 °C to +10 °C - +/− 0.1 °C.Logging rate - 1 reading per 5 minutes.

According to standards, this data logger will be placed in the center of the refrigerator for continuous recording. In practices using more than one refrigerator for vaccine storage, the refrigerator most frequently used and closest to the reception desk will be selected.

#### Self-administered questionnaire (knowledge and temperature monitoring)

The questionnaire will consist of a knowledge part (part 1) and a part addressing current structures and procedures used for monitoring of temperatures (part 2). The knowledge part will be developed drawing on the international body of recognized best practices and guidelines (for example, WHO), official checklists used in other countries (UK, US, and AUS) and previous studies (for example, [12, 14, 16, 17, 20]). Items will correspond to the five educational topics detailed above. In addition, sociodemographic characteristics of physician and practice personnel (sex, age, years in practice/job, part-/full-time, and job content) and practice characteristics (single/group, number of physicians/medical assistants in practice, number of patients quarterly, average number of vaccinations daily, age structure of patients, and urban/rural) will be included. In part two, the current structures and procedures used for the monitoring of temperatures will be obtained. Participants will complete part 1 and 2 of the questionnaire after accessing the web-based program, but before starting with the educational program itself (t1). Follow-up measurements will use a paper-based version of part 1 of the questionnaire, handed out and collected when downloading follow-up data logger readings (t2 and t4). Inspections of temperature logbooks at t2 and t4 will serve as the follow-up measurement for part 2.

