## Methods/design

### Study design

Keep Cool is a prospective, randomized, controlled intervention trial, which will be performed in a random sample of primary care practices (see Fig. 1). After telephone recruitment, all practices will be visited by a study assistant to set up temperature data loggers (t0). Based on continuous temperature recordings over 7 days, all practices with readings outside the target range for vaccine storage (+2 °C to +8 °C) will be randomly allocated (1:1) to an intervention group or a waiting list control group. Practices with temperatures within the target range will be followed separately to monitor temperature fluctuations. Baseline data on knowledge will be collected at t1 prior to the start of the intervention, whereas the compliance with storage recommendations and the assignment of personnel as vaccine storage manager and backup will have already been documented by the study assistant during recruitment (t0). After baseline measurements at t1, the intervention group will receive access to the e-learning program. Follow-up data will be obtained after 6 months (t2) and, to study the intervention’s long-term effectiveness, after 1 year (t3) and 18 months (t4). After the intervention phase is completed, the waiting list control group will receive access to the e-learning program.

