##### Waiting list control group

The control group will consist of practices that have temperature readings outside the target range during baseline data collection. The control group will be monitored via a temperature data logger but will receive access to the e-learning program only after t2. By including a control group, an intervention bias due to the set-up of data loggers is taken into account. The control group is closest to regular everyday care and serves as a baseline to better determine the effectiveness of the intervention.

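### The timing of the t1 questionnaire contradicts itself across sections and leaves controls no stated route to a pre-t2 baseline; the measurement method also changes between baseline and follow-up

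*Protocol article*

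**What the plan says.** All references are to the Protocol article.

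- **Self-administered questionnaire (knowledge and temperature monitoring):** the t1 instruction is "Participants will complete part 1 and 2 of the questionnaire after accessing the web-based program, but before starting with the educational program itself". It covers both parts of the form and makes no exception for either arm. For knowledge, "Follow-up measurements will use a paper-based version of part 1 of the questionnaire", distributed and taken back at the t2 and t4 logger downloads. For monitoring procedures (part 2), the follow-up measurement is an inspection of the practice's temperature logbook. The same questionnaire also carries the staff and practice characteristics.
- **Study design:** "Baseline data on knowledge will be collected at t1 prior to the start of the intervention", and then "After baseline measurements at t1, the intervention group will receive access to the e-learning program". Controls come later: "After the intervention phase is completed, the waiting list control group will receive access to the e-learning program".
- **Waiting list control group:** controls "will receive access to the e-learning program only after t2".
- **Outcomes:** temperature monitoring and knowledge are both secondary outcomes worded as improvement.
- **Statistical analysis:** baseline characteristics are to be described for both arms. Effectiveness is assessed between groups and also within groups, baseline against follow-up: McNemar tests for dichotomous outcomes, paired t-tests for sum scores and the Wilcoxon signed rank test for temperature monitoring.

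**The concern.** A within-arm change test needs a value before the intervention period and a value after it, obtained in the same way. Two things stand in the way.

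First, one section makes entry to the web program a precondition for the baseline form, while another denies controls that entry until the 6-month outcome has been collected. A field team following both would obtain the control questionnaire only after t2, when it is no longer a baseline.

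Second, even where a baseline exists, the follow-up does not repeat the same measurement. A change between t1 and t2 could reflect the change of method rather than a change in the practice.

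At stake are the control arm's within-arm results on two secondary outcomes, the control half of the baseline table, and the interpretation of within-arm change in both arms. A baseline missed in controls cannot be recovered later.

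**Working it through.** **How many practices are concerned.** From Sample size estimation: 46 practices are needed (23 per arm) and dropout is 20 %. 46 / (1 − 0.20) = 57.5, rounded up to 58, which is the plan's figure. With one third of refrigerators out of range, 58 × 3 = 174 practices are recruited for t0, also the plan's figure. With 1:1 allocation, 58 / 2 = 29 practices are controls. So at most 29 of 58 (50 %) would lack a questionnaire baseline under the literal reading.

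**Timing, section by section.**

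| Section | Order of t1 form and access | Consequence for controls |
|---|---|---|
| Self-administered questionnaire | Access to the program first, then the form, then the teaching | Form depends on access |
| Waiting list control group | Access only after t2 | No form before t2 if access is required |
| Study design | Form at t1 first, then access (stated for the intervention arm) | Pre-intervention baseline intended, route not given |

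The first and third rows give opposite orders. The first and second rows together put the control form at 6 months or later. No section describes another way for controls to complete t1.

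**What depends on the t1 value.**

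1. Within-arm tests on knowledge and temperature monitoring: these need a baseline in the arm being tested.
2. Description of staff and practice characteristics for both arms: these items sit in the questionnaire, so the control half depends on t1.
3. Between-arm tests at t2: these are planned as chi-square, t or Mann-Whitney comparisons, and none is described as baseline-adjusted. They do not need a t1 value.
4. Primary outcome, storage checklist and assignment of personnel: these are baselined at t0 by the logger or the study assistant. They do not use this questionnaire, and the sample size rests on the logger outcome.

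**Method at each time.**

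| Outcome | t1 | t2 and t4 | Same measurement? |
|---|---|---|---|
| Knowledge (part 1) | Web form, implied by its place on program entry and by the follow-up being called a paper version | Paper, distributed and taken back at the logger download | Same content, different mode |
| Temperature monitoring (part 2) | Self-report of procedures | Inspection of the logbook | No |

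The second row is the stronger problem. It is explicit in the text, and it remains even if the access conflict is resolved. The Wilcoxon signed rank test for temperature monitoring would pair what staff say they do with what the logbook shows.

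**The case against.** The strongest reply is that the sections can be read together. The questionnaire section itself distinguishes entering the web program from starting the teaching, and what controls are denied is the e-learning. If controls could log in to a platform, complete the form and find the teaching locked, all three statements could hold. The Study design section plainly intends a baseline before the intervention and excludes neither arm. Fig. 1, missing from the text available, may show t1 by arm, and an article may leave the route to a web form to a fuller protocol.

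Part of this stands. The intention is clear, so a reader should not conclude that control baselines are unobtainable; that follows only from the most literal combination of two sections. But no locked-content login is described, the printed orders differ, and a contradiction in the printed text is not merely an omitted detail. A locked login would also leave both changes of method in place.

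Two further replies are correct and limit the point. Both arms use the same method at t2, so the randomised comparison at t2 is like for like. And the follow-up form is self-administered: a reader might infer from its being distributed and taken back at a visit that completion is supervised, but the text does not say so.

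**Conclusion.** The point holds in a limited form. The three sections conflict on when and how the t1 questionnaire is completed and must be reconciled. Under the literal reading, up to 29 of 58 randomised practices have no pre-t2 value for knowledge, temperature monitoring or the questionnaire-based characteristics; under the Study design section alone, a baseline in both arms is possible. Independently of that, the paired baseline-versus-follow-up tests compare different measurements, by mode for knowledge and by kind for temperature monitoring. The direction and size of the resulting distortion cannot be derived from the document.

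Two stronger readings are tempting and are not supported. One is that knowledge and monitoring cannot be compared between arms: randomisation supports comparing the t2 values without a baseline, and that is how the planned between-arm tests are described. The other is that the trial loses the precision of baseline adjustment: no such adjustment is planned, and no correlation between baseline and follow-up is given.

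The matter should be corrected before recruitment, but it concerns secondary outcomes and baseline description only. The conclusion assumes that the t1 form is web-based, which the text implies but does not state; the mismatch in part 2 does not depend on that assumption.

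**What to change.** 1. In the questionnaire section, delete the condition that t1 follows entry to the web program, and bring the wording into line with Study design and Waiting list control group.
2. Have staff in both arms complete the same paper questionnaire after the 7-day baseline logging and before allocation is disclosed, and define that as t1. This gives part 1 one mode throughout, secures the characteristics in both arms, and stops program access from revealing allocation before the form is answered.
3. Measure temperature monitoring at baseline by the same logbook inspection, scored on the same scale, as at t2 and t4. A paper version of part 2 alone would not cure the mismatch. Self-reported part 2 can be kept as description.

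The cost is a little printing, data entry and visit time. Waiting until the 7-day readings are known limits the work to the 58 practices going on to randomisation. Handing the form out at the t0 visit would also serve, but it would collect questionnaires from about 174 − 58 = 116 practices that are never randomised. The article does not say how the 7-day readings are retrieved; if that involves no visit, the form and the logbook inspection need a contact of their own in the 58 practices.

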### Statistical analysis

Descriptive statistics will be used to describe baseline characteristics for both study arms with regard to practice characteristics (single/group, number of physicians/medical assistants in practice, number of patients quarterly, average number of vaccinations daily/per week, age structure of patients), participating physician and practice personnel characteristics (sex, age, years in practice/job, part-time/full-time, job content). The effectiveness will be assessed by comparing the intervention and control group and by intragroup comparison (baseline versus follow-up). We will evaluate the effectiveness based on temperature as the main outcome (within range yes/no) by comparing both groups using the chi-square test. For intergroup analyses, all dichotomous secondary outcomes will be evaluated using chi-square tests for each item. In addition, compliance with storage recommendations will be analyzed on the basis of a sum score calculated across all items by using a t-test. For in-group comparisons, McNemar tests will be calculated for dichotomous outcomes and t-tests for dependent samples for sum scores. Temperature monitoring will be measured on an ordinal level to allow for application of the Mann-Whitney U Test (intergroup comparison) and the Wilcoxon signed rank sum test (intragroup comparison). A *P* value <0.05 will be considered significant. All statistical analyses will be performed using IBM SPSS 22® on Windows.

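### Temperature monitoring is self-reported at baseline but inspected at follow-up, so the planned within-arm test of improvement mixes a change of instrument with a change of behaviour

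*Protocol article*

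**What the plan says.** Temperature monitoring is the first-listed secondary outcome. Under Outcomes it is framed as an improvement, and the optimal level requires "electronic or paper-based recording with a minimum of two readings per day for the previous 5.5 months"; up to 5 % of entries may be absent. The behaviour meant is "temperature monitoring, including temperature reviewing, recording, taking immediate action if needed and retention of temperature logs".

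The section on the self-administered questionnaire gives the source at each time point. At baseline: "Participants will complete part 1 and 2 of the questionnaire after accessing the web-based program, but before starting with the educational program itself (t1"). On the content of that part: "In part two, the current structures and procedures used for the monitoring of temperatures will be obtained". At follow-up: "Inspections of temperature logbooks at t2 and t4 will serve as the follow-up measurement for part 2".

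Under Statistical analysis, the outcome is ordinal. Arms are compared by the Mann-Whitney U test, and baseline is compared with follow-up inside each arm by "the Wilcoxon signed rank sum test (intragroup comparison").

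**The concern.** A signed rank test of improvement is meaningful only if both members of each pair are measured in the same way. Here the first is an individual's account of procedures and the second is an examined practice record. The difference between them has two components: what the practice changed, and how far self-report departs from inspection. The test cannot separate them.

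The direction can be foreseen. If staff overstate their record-keeping at t1, inspection at t2 or t4 will show fewer adequate logs even where nobody has changed, and real gains will be understated. This matters because the Background section names lasting routines for daily temperature monitoring as the structural change that educational programmes need. A within-arm result that shows no gain, or a loss, could be read as failure of that mechanism when it only reflects the switch of instrument.

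**Working it through.** **Passages side by side**

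| | Baseline | Follow-up |
|---|---|---|
| Temperature monitoring | Self-administered questionnaire, part 2 (t1) | Logbook inspection (t2, t4) |
| Storage compliance | Checklist by study assistant (t0) | Same checklist by study assistant (t2, t3, t4) |

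The second row comes from the Storage checklist section. The protocol keeps one instrument for storage compliance and changes it for temperature monitoring.

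**Size of the shift**

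The article gives no power or sample size for this outcome, so there is no stated figure to reproduce. The only figure taken from the sample size section is the arm size of 23.

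For simplicity, cut the ordinal scale once, into adequate records or not. Let p be the true proportion with adequate records, and o the probability that a practice without them reports having them. Both are assumptions. I take p = 0.30, and p = 0.51, the complement of the 49 % without a temperature log in the survey cited in the Background. I take o = 0.20 and 0.40.

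Apparent baseline = p + (1 − p)·o. With no true change, follow-up = p. The spurious fall is (1 − p)·o, which is also the true improvement that would be cancelled.

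| p | o | Apparent baseline | Spurious fall | Expected false falls among 23 |
|---|---|---|---|---|
| 0.30 | 0.20 | 0.44 | 14.0 points | 3.2 |
| 0.30 | 0.40 | 0.58 | 28.0 points | 6.4 |
| 0.51 | 0.20 | 0.608 | 9.8 points | 2.3 |
| 0.51 | 0.40 | 0.706 | 19.6 points | 4.5 |

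**How often would this be declared a change?**

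With no true change, all discordant pairs point downwards. For b such pairs, the exact two-sided paired test has P = 2 × 0.5^b. This is 0.0625 for b = 5 and 0.031 for b = 6, so significance needs b ≥ 6. The false-change rate is P(Binomial(23, (1 − p)·o) ≥ 6):

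- o = 0: 0 %
- o = 0.20: 2.1 % (p = 0.51) to 9.2 % (p = 0.30)
- o = 0.40: 28.8 % (p = 0.51) to 65.8 % (p = 0.30)

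A simulation of 4,000 trials per setting agreed: 3 to 9 % and 29 to 66 %.

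The planned test is the Wilcoxon. If every fall is one level, all ranks tie: W = b(b+1)/2, its mean is b(b+1)/4, and its tie-corrected variance is b(b+1)²/16. Then z = √b, and the large-sample version needs only b ≥ 4. On that version the rates are 18 to 41 % at o = 0.20 and 69 to 92 % at o = 0.40.

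**Between arms at t2**

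The same inspection is described for both arms. In the simulation, with no true arm difference and a chi-square test on the same single cut, rejection stayed at about 4 to 6 % at every over-reporting rate tried. The baseline questionnaire does not enter this comparison.

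**The case against.** The strongest reply is that the effect is confined. It touches a supplementary within-arm analysis of one secondary outcome, the randomised comparison stays sound, and the bias would hide benefit rather than create it. Its size also rests wholly on assumed over-reporting: with none, there is no false change. All of this stands. It limits the weight of the point but does not remove it, because the article itself fixes both the two instruments and the paired test; this is not detail left to a fuller document.

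A reader might infer three stronger things that the documents do not support.

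- *That the between-arm test also measures the instrument.* It does not. One follow-up method is described, with no difference by arm.
- *That the trial's own logger satisfies the definition in every practice.* Electronic recording is accepted, and the logger, at 288 readings a day, would give about 48,200 readings over 5.5 months (about 167 days) against about 335 required. But the outcome is read from logbooks, which the questionnaire section names separately from logger downloads. The Intervention section describes staff reviewing a standard thermometer and writing in a temperature log. The practice's own record is the natural reading; only an express exclusion is absent.
- *That a paper log cannot meet the rule because practices close at weekends.* Closing two days in seven would lose about 96 of 335 entries, against about 17 allowed. But the article states neither closing days nor that closed days count as missing, and only the top level of an ordinal scale is affected.

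**Conclusion.** The point holds for the within-arm baseline-to-follow-up comparison of temperature monitoring, and only there. That test pairs self-report with inspection, so its result cannot be read as behaviour change. Under the assumptions used (over-reporting of 20 to 40 % among practices without adequate records, true rates of 30 to 51 %), 10 to 28 percentage points of real improvement would be offset. The direction follows from over-reporting; the amount is unknown. The false-change rates also depend on cutting an ordinal outcome once, or on one-level falls for the Wilcoxon version.

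The Mann-Whitney comparison at t2 is not affected. The logger and closed-day questions are wording to clarify, not established defects. The correction is worth making because it is cheap, but nothing in the primary outcome or the sample size depends on it.

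**What to change.** Have the study assistant inspect the practice's own logbook at the t0 visit and code it on the same ordinal scale as at t2 and t4. Use that coding as the baseline for the Wilcoxon test; part 2 of the questionnaire can stay as description. Name the between-arm comparison at t2 as the main analysis of this outcome.

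The study assistant already visits at t0 and completes the storage checklist then, so no new visit or staff are needed, and the coding is done before allocation. The cost is a few extra minutes per visit. Because t0 precedes selection, this includes practices that are never randomised: 174 are to be recruited to find 58 with readings out of range, so 174 − 58 = 116 of the inspections would not serve the randomised comparison.

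As clarification only, add one sentence saying that study-logger recordings do not count as practice recording, and whether days when the practice is closed count as missing entries.
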